## Abstract

**Background:**

Office-based workers typically spend 70–85% of working hours, and a large proportion of leisure time, sitting. High levels of sitting have been linked to poor health. There is a need for fully powered randomised controlled trials (RCTs) with long-term follow-up to test the effectiveness of interventions to reduce sitting. This paper describes the methodology of a three-arm cluster RCT designed to determine the effectiveness and cost-effectiveness of the SMART Work & Life intervention, delivered with and without a height-adjustable desk, for reducing daily sitting.

**Methods/design:**

A three-arm cluster RCT of 33 clusters (660 council workers) will be conducted in three areas in England (Leicester; Manchester; Liverpool). Office groups (clusters) will be randomised to the SMART Work & Life intervention delivered with (group 1) or without (group 2) a height-adjustable desk or a control group (group 3). SMART Work & Life includes organisational (e.g., management buy-in, provision/support for standing meetings), environmental (e.g., relocating waste bins, printers), and group/individual (education, action planning, goal setting, addressing barriers, coaching, self-monitoring, social support) level behaviour change strategies, with strategies driven by workplace champions. Baseline, 3, 12 and 24 month measures will be taken. Primary outcome: Objectively measured daily sitting time (activPAL3). Secondary outcomes: objectively measured sitting, standing, stepping, prolonged sitting and moderate-to-vigorous physical activity time and number of steps at work and daily; objectively measured sleep (wrist accelerometry). Adiposity, blood pressure, fasting glucose, glycated haemoglobin, cholesterol (total, HDL, LDL) and triglycerides will be assessed from capillary blood samples. Questionnaires will examine dietary intake, fatigue, musculoskeletal issues, job performance and satisfaction, work engagement, occupational and general fatigue, stress, presenteeism, anxiety and depression and sickness absence (organisational records). Quality of life and resources used (e.g. GP visits, outpatient attendances) will also be assessed. We will conduct a full process evaluation and cost-effectiveness analysis.

**Discussion:**

The results of this RCT will 1) help to understand how effective an important simple, yet relatively expensive environmental change is for reducing sitting, 2) provide evidence on changing behaviour across all waking hours, and 3) provide evidence for policy guidelines around population and workplace health and well-being.

**Trial registration:**

ISRCTN11618007. Registered on 21 January 2018.

## Background

Technological innovations and economic advances have led to increases in physical inactivity and sedentary behaviour [1]. Evidence indicates that it is not only important to be physically active for at least 150 min a week, but also to limit the number of waking hours spent being sedentary (i.e., sitting). A wealth of epidemiological evidence now exists that demonstrates that sedentary behaviour is associated with an increased risk of poor metabolic health [2] and chronic disease (type 2 diabetes, cardiovascular disease, some cancers and mortality) [3–6], often independently of BMI and physical activity.

Office workers are one of the most sedentary populations, with data showing that they spend 70–85% of time at work sitting, with over a third of total sitting time being accumulated in bouts of prolonged, unbroken sitting of 30 min or more [7]. Additionally, research has shown that workers who spend large proportions of their time sitting at work also spend more time sitting during leisure time than their less sedentary counterparts [8]. A small number of epidemiological studies using isotemporal substitution analysis have shown that substituting sitting time for standing and stepping was beneficially associated with markers of cardiometabolic health such as glucose, insulin, and inflammation [9–11]. Furthermore, a rapidly growing body of acute experimental evidence demonstrates that avoiding long bouts of sitting by incorporating short (e.g., 2–5 min) but frequent (e.g., every 20-30 min) bouts of more light intensity movement (standing and stepping) improves glucose, insulin, blood pressure and fatigue levels [12–18]. Such sitting reduction strategies have also been shown to reduce musculoskeletal (e.g., low back) discomfort in office workers [19].

Recent evidence suggests that high levels of moderate-to-vigorous physical activity (MVPA), for example at least 60–120 min per day, may offset the increased mortality risks associated with high levels of total sitting time (> 8 h/day) [20, 21]. However, the high levels of activity needed to be protective are unlikely to be achievable for most of the population. Indeed, a recent study of one million adults showed that 75% do not undertake this amount of MVPA [21]. Therefore, a first “behavioural” step could be to simply get people standing and moving more frequently as part of their day.

A review was published in 2016, and updated in 2018, summarising the effectiveness of workplace interventions for reducing sitting time at work [22, 23]. These interventions included physical workplace changes such as providing height adjustable desks to enable sitting or standing at work, pedalling workstations and treadmill desks, policy changes, information provision and counselling, and computer prompts. Providing height-adjustable workstations was the most frequently implemented intervention and was reported as the most promising for reducing sitting time at work (average reduction of 100 min/work day in the short term, 57 min/work day in the medium term) [23]. Whilst positive findings were observed, the review concluded that the quality of evidence was low to very low for most studies mainly because studies were poorly designed; for example, there was a lack of non-biased cluster randomised controlled trials, and generally small samples. They also concluded that ‘there is a need for larger cluster-randomised trials with longer term follow-up’.

To date only a handful of studies currently address these limitations [24, 25] and only one ongoing study, albeit that does not include a control group, has a follow up beyond 12 months [26]. The Stand More AT Work (SMArT Work) multi-component intervention was evaluated through a large cluster RCT with follow up at 3, 6 and 12 months [24, 27]. Although SMArT Work was successful in reducing sitting time at work et all follow up time points, results suggested that no changes in sitting outside of work were made as reductions seen for daily sitting time were similar to those observed during work hours [27]. Similarly, the Stand Up Victoria trial also observed significant changes in sitting time across the day, but findings suggested that this was also predominantly driven by workplace changes, rather than changes during non-work time [28]. To maximise the potential health benefits of reducing sitting time there is a need for interventions to take a ‘whole of day’ approach to behaviour change, and focus not only on workplace sitting time, but also on sitting outside of work.

In recent years, interventions focused on reducing sitting time in the workplace have involved providing the employee with a height-adjustable workstation to enable them to sit or stand to perform their work tasks. As mentioned previously, evidence indicates that this type of intervention shows promise for helping employees to reduce their sitting time [22, 23]. However, this piece of equipment is relatively expensive. Moreover, while the recent systematic review of workplace interventions suggests that greater reductions in sitting are seen with interventions involving height-adjustable workstations in comparison to interventions that do not (e.g., information provision and counselling), a direct comparison of a sitting reduction intervention with and without the provision of a height-adjustable workstation has not been conducted within a single, large, robustly designed study. This is an important next step as it will allow researchers and employers to understand the importance of providing a simple, but relatively expensive environmental change for significant reductions in sitting. One active research trial in the US is evaluating the efficacy of a multilevel intervention with (STAND +) and without (MOVE +) the provision of sit-stand workstations and although a large randomised trial, it does not include a control group [26].

### Aims and objectives of the study

#### Aim

The aim of this study is to determine the long-term effectiveness and cost-effectiveness of the multi-component SMART Work & Life intervention (when provided with and without a height-adjustable workstation) for reducing daily sitting time in office workers compared with no intervention. If both interventions are shown to be effective, a secondary aim will be to determine if one intervention is more effective than the other. SMART Work & Life is a refined and extended version of the previously evaluated SMArT Work intervention [24, 27].

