### Sample size

The primary analysis will be performed using linear multilevel models, which require a minimum of 10 clusters per arm in order to robustly estimate random effects [29]. Power calculations indicated that with a sample size of 10 clusters per arm and an average cluster size of 14, this study would have over 90% power to detect a 60 min reduction in overall sitting time with a two-tailed significance level of 5%. The calculations assumed a standard deviation of 90 min (informed by SMArT Work, [27]), a conservative intraclass correlation coefficient (ICC) of 0.05 (informed by Stand Up Victoria, [28]), a coefficient of variation to allow for variation in cluster size of 0.54. These calculations allowed for multiple comparisons against the control group. The number of clusters per arm has been inflated by 1 to allow for whole cluster drop out and the sample size was also inflated by 30% to allow for potential individual loss to follow-up and non-compliance with the primary outcome (inflating the n per cluster from 14 to 20). This gives a total sample size of 660 to be recruited, with 11 clusters per arm. Finally, the sensitivity of power was assessed against alternative ICC values of 0.021 and 0.10 [28]. Adequate power for RCTs is widely accepted as 80%, and with these ICC values the power was above the required level at 98 and 81%, respectively.

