*Individual and group strategies* grounded in Social Cognitive Theory, Self-Regulation Theory and Relapse Prevention Theory (targeting ‘capability, ‘motivation’ & ‘opportunity’ through BCW intervention functions: enablement, persuasion, education and training): 1) An initial online education session which covers health consequences of sitting and benefits of reducing and regularly breaking up sitting. The session encourages participants to estimate their own sitting time, brainstorm strategies to reduce sitting at work and outside of work, consider barriers to reducing and breaking up sitting and ways to overcome these barriers. At the end of the session individuals will be encouraged to set a goal around sitting less and an action plan to achieve this. The focus on overall daily sitting will be emphasised rather than just workplace sitting; 2) Self-monitoring of sitting behaviour across the whole waking day will be encouraged through the use of free computer prompts, timers and mobile phone apps. For example, the Rise & Recharge app. The importance of self-monitoring and prompts will be introduced during the education session and the choice of apps, computer software and prompts will be presented during the session; 3) Workplace champions will receive training to encourage their colleagues, deliver brief group coaching, implement competitions and send emails. The coaching sessions will be used to discuss progress, review goals and action plans, discuss personal or social barriers and any benefits experienced. These coaching sessions will take place four times during the intervention period; 4) Workplace champions will send out monthly motivational/education emails; 5) Social support, from colleagues and family members, will be encouraged through regular activity competitions inside and outside of work.

#### Intervention arms 1 and 2

Both intervention arms will receive all of the intervention components listed in the previous sections. However, intervention arm 2 will not receive a height-adjustable workstation. By having both intervention arms receive the same intervention with the exception of the workstation will allow us to investigate how important providing this component is for reducing sitting.

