### Statistical analysis

#### Primary and secondary outcomes

The aim of the primary analysis is to investigate the impact of the multi-component intervention (SMART Work & Life), with and without a height-adjustable workstation, on objectively measured daily sitting time compared to usual practice at 24-month follow-up. The primary outcome analysis is powered to detect a significant difference in sitting time of 60 min/day at 24 months. However, discontinuation of the study due to futility will be considered in a formal interim analysis at 12 months. An Independent Data Monitoring Committee (DMC) will be convened to review the primary outcome at 12 months. The conditional probability of the final study results being statistically significant given the data observed at 12 months will be calculated and the DMC will make a recommendation based on this and other important factors (i.e. trial conduct, data quality, participant retention) of whether or not to continue follow-up until 24 months. If the DMC decide the data from the interim analysis at 12 months provides satisfactory evidence to continue, the trial will continue to follow-up participants to 24 months. Furthermore, only if both arms are determined to be futile at the interim analysis stage will the trial be stopped early.

The primary analysis will be performed using a linear multilevel model with sitting time as the outcome variable. Levels to indicate the clustering of workers within office sites, a categorical variable for randomisation group as the explanatory variable (control will be the reference group and will be compared to intervention 1 and intervention 2), and terms for the stratification factors (area and cluster size), baseline values and device wear time will be confounders. In these linear multilevel models, office clusters will be incorporated as a random effect to model worker heterogeneity within office sites. The structure of the variance-covariance matrix for the random effect will be assumed to be unstructured and the models will be estimated using restricted maximum likelihood. For the primary analysis, missing data will not be replaced (complete case analysis) and participants will be included in the intervention group in which their clusters were randomised irrespective of the intervention that was actually received.

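### The direct desk versus no-desk comparison is planned only if both interventions beat control, although it is presented elsewhere as a main purpose of the three-arm design

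*Protocol article*

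**What the plan says.** The Aim of the protocol article sets the comparison of the two interventions behind a condition: "If both interventions are shown to be effective, a secondary aim will be to determine if one intervention is more effective than the other".

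Three other places describe the same comparison with no condition:

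- **Background.** It identifies the evidence gap: "a direct comparison of a sitting reduction intervention with and without the provision of a height-adjustable workstation has not been conducted" within one large, robust study. It goes on: "This is an important next step as it will allow researchers and employers to understand the importance of providing a simple, but relatively expensive environmental" (the sentence continues).
- **Intervention arms 1 and 2.** The arms are the same apart from the workstation, and this "will allow us to investigate how important providing this component is for reducing sitting".
- **Abstract, Discussion.** The first listed contribution of the trial is to "help to understand how effective an important simple, yet relatively expensive environmental change is for reducing sitting".

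Under Statistical analysis, Primary and secondary outcomes, one multilevel model contains all three arms, and the named contrasts are those with control: "control will be the reference group and will be compared to intervention 1 and intervention 2". No section provides for the direct comparison when only one intervention is shown effective.

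**The concern.** The condition fails most often when the desk's contribution is largest. If the programme works only with a desk, the no-desk arm will usually not beat control, and the stated aim of comparing the two interventions then lapses. What remains is one significant and one non-significant contrast with control. That pattern does not test the difference between the arms and gives no interval for it.

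A second issue arises when the condition is met. Requiring the weaker arm to pass a significance threshold selects trials in which that arm did well by chance. If the no-desk effect is truly small to moderate and below the desk effect, the estimated increment in those trials is pulled toward zero.

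At stake is the quantity that the Background says employers need: how much an expensive piece of equipment adds to the programme.

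**Working it through.** **Inputs (Sample size section).** The calculation is "with a sample size of 10 clusters per arm and an average cluster size of 14", with SD 90 min, ICC 0.05, coefficient of variation of cluster size 0.54, target difference 60 min, two-sided 5%, and an allowance for two comparisons with control. The form of that allowance is not stated. I take 2.5% per comparison, an assumption that comes close to the stated powers.

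**Reproducing the stated power.**

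- Design effect = 1 + ((CV² + 1)m − 1) × ICC = 1 + ((0.54² + 1) × 14 − 1) × 0.05 = 1.854.
- Effective n per arm = 140 / 1.854 = 75.5.
- SE of a two-arm contrast = 90 × √(2 / 75.5) = 14.65 min.
- Power for 60 min at two-sided 2.5%, noncentral t with 18 df: 94.1%. The article says over 90%.
- The same steps at ICC 0.021 and 0.10 give 98.6% and 81.8%. The article says 98% and 81%.

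The sample size is not in error. By design, 14.65 min is also the SE of the desk versus no-desk contrast.

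**How often the condition is met.** I simulated 2 million trials per scenario. The three arm means were independent and normal, each with SE 14.65 / √2 = 10.36 min, and both interventions shared the control arm. The condition is met if both reductions exceed the critical t times 14.65. With 18 df that threshold is about 35.8 min at 2.5% and 30.8 min at 5%. The true effects are assumptions, because the documents give none for the no-desk arm separately.

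| True reduction, desk / no desk (min) | Condition met, α 2.5% / 5% | Mean desk contrast when met (min) | True contrast (min) |
|---|---|---|---|
| 60 / 0 | 0.7% / 1.8% | about 40 / 42 | 60 |
| 60 / 20 | 14% / 23% | 28.5 / 30.4 | 40 |
| 60 / 30 | 34% / 48% | 22.4 / 24.0 | 30 |
| 60 / 45 (2.5% only) | 72% | 12.3 | 15 |
| 60 / 60 (2.5% only) | 91% | 0 | 0 |
| 90 / 60 (2.5% only) | 95% | 29.2 | 30 |

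At 60 versus 30, only the desk arm is significant in 61% of trials (α 2.5%) or 50% (α 5%).

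**Sensitivity.** With 27 df, for three arms of 10 clusters in one model, the condition at 60 versus 30 is met in 37% or 50%. Normal critical values give 42% or 53%. With normal critical values at α 2.5%, moving the ICC from 0.021 to 0.10 changes the 60 versus 30 figure from 56% to 29%, and the conditional mean from 25.6 to 20.5 min.

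**Without the condition.** The contrast is always estimated and carries no selection bias. Its power for a 30 min difference at two-sided 5% is about 49% (t, 18 df) to 54% (normal), so about 50%.

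**The case against.** The strongest defence is that this is ordinary hierarchical testing. The Aim speaks of determining whether one intervention is more effective, which can be read as gating a formal claim, and comparing two active arms only after both beat control is a recognised order. Named contrasts and testing order are also commonly left to an analysis plan, and none is shown. This has force: the analysis section's silence on the direct contrast would not be a finding by itself. But the Aim does more than leave the matter open. It states a condition on the comparison, and that condition conflicts with the unconditional purpose given in three other places. Gatekeeping can justify withholding a confirmatory p-value. It gives no reason to withhold an estimate and its interval.

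Three stronger readings are tempting and are not supported:

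- **A reader might infer that the plan yields no estimate at all of the desk effect.** Both arms are in one model with the same control, and estimates are to be given with 95% CIs. Subtracting the two reported coefficients gives the point difference. What is not assured is its interval and test.
- **A reader might infer that the comparison, when made, is always biased toward zero.** The bias depends on the true effects. It vanishes when they are equal and is negligible when both are large. The article's goal and powered effect is 60 min, and with both arms at 60 the condition is met in 91% of trials with no bias. At 60 versus 30 the bias is 6 to 8 min, about half of one standard error.
- **A reader might infer that the economic evaluation has the same fault.** The Cost effectiveness section costs the programme with and without the desk and does not restrict comparisons to each arm against control.

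**Conclusion.** The point stands in this limited form. The condition in the Aim contradicts the article's own rationale, and it removes the planned direct comparison in the situation where the desk matters most. With the article's SD, ICC, cluster numbers and cluster-size variation, the condition is met in about 34% to 50% of trials at assumed effects of 60 and 30 min (α 2.5% to 5%, 18 to 27 df), and in about 1% to 2% at 60 and 0. The conditional estimate is pulled toward zero only when the no-desk effect is small to moderate and below the desk effect: about 22 to 24 min against a true 30.

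The percentages rest on assumed true effects and on approximate degrees of freedom; the direction does not change over the ranges tried. The primary objective, the sample size and the two tests against control are unaffected. A fuller protocol or analysis plan may already provide the contrast, but the condition as published should not stand.

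**What to change.** - In the Aim, delete the condition, so that comparing the two interventions is a secondary aim whatever the contrasts with control show.
- In the statistical analysis section, name intervention 1 minus intervention 2 at 24 months, with its 95% CI, as a secondary contrast from the primary multilevel model, always reported.
- If the desk comparison is to have a formal place in the multiplicity scheme, gate only its p-value.
- State that the trial is not formally powered for this contrast: about 50% power for a 30 min difference at two-sided 5%, with SE about 14.65 min. A non-significant result should not be read as showing that the desk adds nothing.

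The cost is a change of wording. The contrast comes from the model already planned, with no extra participants, measurements or model fits. The change should be made before outcome data by arm are seen.

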#### Primary objective

To investigate the impact of SMART Work & Life, delivered with and without a height adjustable workstation, on objectively measured daily sitting time compared to usual practice at 24-months follow-up.

